### Statistical analyses

#### Overview of analytic plan

We will use standard analytic methods for randomized controlled trials [52]. After comparing baseline characteristics of intervention and control group participants, and accounting for missing data, outcomes will be compared between the two groups. Though we have made unidirectional hypotheses, to allow for the chance that participants enrolled to the control group could have better outcomes than those in the intervention arm, we will use 2-tailed tests of significance for all analyses.

#### Multiple comparisons [53]

We have a priori selected the outcome of change in steps/day to be the primary endpoint of interest. Analyses of all other outcomes will be adjusted for multiple comparisons [54].

#### Intention to treat

All analyses will be conducted using intention to treat, in which any subject randomized to the intervention arm remains in that arm regardless of whether or not he or she received the intervention, and likewise for the control arm. We will measure level of participation for those randomized to the intervention arm, and will conduct a sensitivity analysis that assesses the stability of the study’s conclusions when an intention to treat analysis versus an analysis that takes into account level of participation in the intervention.

#### Comparing baseline characteristics of intervention and control arm subjects

Using t-tests for continuous variables and chi-square tests for categorical variables, we will compare the two groups on baseline characteristics to measure the success of the randomization: 1) sociodemographic characteristics; 2) mean steps/day over 1 week in the window post screening and distribution of pedometers, to the T0 baseline data collection one week later; 3) systolic blood pressure, body mass index, non-HDL cholesterol, HgA1c; 4) stroke knowledge, self-efficacy. Since steps/day is a continuous variable, at each time-point (30 days/T1 and 90 days/T2) we will perform a simple descriptive cross-sectional analysis of mean change in scores between baseline and follow-up in each treatment arm. In our primary analyses, we will test the statistical significance of the unadjusted difference in change-scores between the groups using t-tests for symmetrically distributed data and analogous nonparametric tests such as the Wilcoxon sign rank tests for data that are skewed. Imbalance between the treatment arms of characteristics described above would inflate the standard error, making the unadjusted analyses appropriately conservative; therefore, the unadjusted analyses will serve as the primary results of the trial. If, however, we did identify chance differences between the treatment arms in the distribution of the baseline level of the outcome, then we will also conduct secondary analyses in which we will use multivariate modeling, such as analysis of covariance, to adjust for these factors. The adjusted means of the change-scores from multivariate models will be compared and tested between the two arms, and will also be compared with the unadjusted means to assess the influence of these factors on endpoints. As sensitivity analyses, we will also examine the difference between groups in the absolute steps/day (instead of the change-score), adjusting for baseline. These sensitivity analyses will allow us to compare outcomes between groups without assuming linearity of effect across different baseline levels of physical activity. Using multivariate modeling, we will also test interactions between treatment arm and selected effect modifiers (e.g., age, level of acculturation, etc.) to identify sub-groups of participants who improve more than other groups. Since this trial is not designed with power to examine these subgroups, these analyses will be exploratory and hypothesis-generating in nature. Finally, we will assess changes in steps/day between baseline and the end of the intervention period, and differences between the control and intervention groups in steps/day trajectories over time. These analyses will consist of graphical analysis and parametric statistical testing using repeated measures mixed effects models [55, 56]. To determine the extent to which increases in stroke knowledge and self-efficacy mediate improvements in steps/day, the variation (R-squared) in increase in steps/day is explained by variation in increase in the stroke knowledge and self-efficacy constructs will be calculated [57, 58]. Analysis of the effect of the intervention on all the secondary and exploratory outcomes will follow the same analysis.

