**Methods/Design:**

In this randomized single-blind wait-list control study, high-risk ethnic minority seniors are enrolled at senior centers, complete baseline data collection, and are randomly assigned to receive the intervention “Worth the Walk” immediately (*N* = 120, intervention group) or in 90 days upon completion of follow-up data collection (*N* = 120, control group). Trained case managers employed by the senior centers implement hour-long intervention sessions twice weekly for four consecutive weeks to the intervention group. Research staff blinded to participants’ group assignment collect outcome data from both intervention and wait-list control participants 1 and 3-months after baseline data collection. Primary outcome measures are mean steps/day over 7 days, stroke knowledge, and self-efficacy for reducing stroke risk. Secondary and exploratory outcome measures include selected biological markers of health, healthcare seeking, and health-related quality of life. Outcomes will be compared between the two groups using standard analytic methods for randomized trials. We will conduct a formal process evaluation to assess barriers and facilitators to successful integration of Worth the Walk into the aging services network and to calculate estimated costs to sustain and scale up the intervention. Data collection is scheduled to be completed in December 2016.

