#### Randomization & blinding

After baseline data have been collected and participants have dispersed, we utilize a computerized randomization procedure stratified by site and gender to assign participants to either the intervention or the control (wait-list) arm. The randomization procedure is programmed into Research Electronic Data Capture (REDCap), a secure web application for building and managing online surveys and databases [32]. A randomization allocation table was created using random permuted blocks with randomized block sizes 2, 4, 6 and is uploaded into REDCap. Smaller block sizes are used to distribute participants within either group as evenly as possible.

One designated research assistant is un-blinded for the duration of the study and works with senior center staff to schedule the WTW intervention sessions. Senior center staff call participants to inform them of their scheduled intervention session. While the case manager group leaders administer WTW, the same un-blinded research assistant attends sessions to take attendance and monitor fidelity to the curriculum using a standardized checklist of all the major teaching points of each intervention session (see Additional file 1: Appendix A). Other (blinded) project staff members maintain regular telephone contact with participants in both arms of the study to remind them to wear their pedometers but without explicitly prompting physical activity or walking. Project staff who are in the field collecting data are blinded to the participant assignment group for the entire study duration.

All participants in both the intervention and control groups receive the same frequency of contact from study staff (phone call reminders) and the same incentives (pedometers, $25 visa gift card at each data collection time point). We do not refer to the control group as a “wait-list” when speaking with participants and agency staff, but rather refer to that group by the month in which they will start the WTW program, for example, we will compare the “January” group with the “April” group.

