### Sample size and power

As described above, our primary outcome of interest is change in mean steps/day, while our main secondary outcome measure is change in systolic blood pressure. Based on our capacity, we plan to enroll 240 subjects from 4 senior centers. From our previous senior center research we estimate that as many as 15 % of subjects will not complete follow-up. Data from our previous senior center studies of older Latinos and African Americans showed mean steps/day 2713 (std. dev. 2190) and mean SBP 141 mm Hg (std. dev. 20 mm Hg); intra-class correlation within senior centers was at 0.0085. Since we propose a repeated measures design with 3 repeated measurements [46], the underlying statistical power of the study comes from two dimensions of observations: the number of unique subjects and the number of repeated measurements within a subject. Based on sample size/power analytic methods for repeated measures analysis [47, 48], using a 2-sided test with a type I error of 0.05, and a type II error of 0.2 (power 80 %), and assuming an average 2.7 data points per subject and an auto-correlation at 0.2 level, after adjusting for clustering, the effective sample size will be 96 subjects in each arm, which will enable us to detect effect sizes as small as 581 steps/day (far below a clinically meaningful increase of 5000 steps/day [49]) and 5.3 mm Hg. A decrease of 5 mm Hg substantially decreases stroke risk [50] and is comparable to effect sizes observed in walking interventions of similar intensity [51].

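### The nonparametric fallback named for the between-arm comparison of change-scores is the Wilcoxon signed-rank test, a one-sample or paired test that does not fit two independent arms

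*Protocol article*

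**What the plan says.** The analysis is set out in the protocol article under *Comparing baseline characteristics of intervention and control arm subjects*. For the primary analysis it states that "we will test the statistical significance of the unadjusted difference in change-scores between the groups using t-tests for symmetrically distributed data", and for skewed data it gives "analogous nonparametric tests such as the Wilcoxon sign rank tests for data that are skewed".

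The same section gives this analysis its rank: "the unadjusted analyses will serve as the primary results of the trial". It also extends it: "Analysis of the effect of the intervention on all the secondary and exploratory outcomes will follow the same analysis".

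Under *Randomization & blinding*, allocation is by a "computerized randomization procedure stratified by site and gender to assign participants to either the intervention or the control (wait-list) arm", with random permuted blocks. No participant in one arm is matched to a participant in the other. The rank-sum (Mann-Whitney) test is not named anywhere in the article.

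**The concern.** The sentence sets a two-sample task and then names a one-sample or paired test for it. The t-test half is sound. The fallback half names a procedure whose null hypothesis does not involve the contrast between arms.

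This matters because of where the sentence stands. It governs the primary result for steps/day and, by extension, every secondary and exploratory outcome whose change-scores turn out skewed. A test is named in advance so that nobody has to choose one after seeing the data. If the named test cannot be used as written, the analyst must pick a substitute at that stage.

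**Working it through.** No figure in the plan depends on this point. The inputs listed under *Sample size and power* (standard deviations, intra-class correlation, loss to follow-up, data points per subject, autocorrelation, type I and type II error) do not include the fallback test. The check is therefore one of logic.

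**Notation.** Let X₁…Xₙ be the change-scores in the intervention arm and Y₁…Yₘ those in the control arm. With 120 per arm and the plan's 15 % loss, n = m = 120 × 0.85 = 102 if loss is equal in the two arms.

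**Signed-rank test.** It ranks the absolute changes in one set and sums the ranks of the positive ones (W⁺). Its null is that this set is symmetric about zero, with expectation n(n+1)/4 = 102 × 103/4 = 2626.5 and maximum n(n+1)/2 = 5253.

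**Rank-sum test.** It counts the pairs (i, j) in which Xᵢ exceeds Yⱼ (U). Its null is that both arms have the same distribution of change, with expectation nm/2 = 102 × 102/2 = 5202.

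**Which one measures the arm difference?** Add a constant c to every change in both arms, so that the treatment contrast is untouched.
- Every Xᵢ − Yⱼ is unchanged, so U is unchanged.
- W⁺ rises with c. Once c exceeds the size of the largest fall, W⁺ reaches its maximum of 5253.

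The signed-rank statistic thus responds to change common to both arms. The rank-sum statistic responds only to a difference between them.

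**Could the signed-rank test be applied here in any way?**
1. *Within one arm:* it tests whether that arm changed.
2. *On both arms pooled:* it tests whether participants as a whole changed.
3. *Across arms, by pairing participants arbitrarily:* it would then concern the contrast. However, the result would depend on an arbitrary pairing, the numbers per arm would have to be equal, and information would be lost. The design supplies no pairing, and nothing makes the numbers of completers equal.

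**Fit to skewed data.** The signed-rank null includes symmetry about zero. A skewed set of changes with mean zero does not satisfy it, so rejection may reflect shape alone. The test is ill-suited to the very condition that triggers it.

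**The case against.** The best defence is that this is a slip of naming. The sentence fixes the target as a difference between groups, asks for an analogue of the t-test, and gives its example only as one of a kind. The nonparametric analogue of a two-sample t-test is the rank-sum test, and a competent analyst would probably use it. A separate analysis plan, not shown here, may already name it. The article's other between-arm analyses (baseline-adjusted absolute steps/day and mixed models of trajectories) do not use the signed-rank test, although they are not primary. All of this stands and lowers the likely harm. It does not make the named test right.

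Three stronger readings are tempting, and the documents do not support them.

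- *A reader might infer that efficacy would be judged by significance in one arm and not in the other, or by a pooled test, and attach an inflated false-positive rate.* The article calls within-arm change a descriptive analysis and nowhere pools the arms for testing. Such a rate would also need a common rise and a standard deviation of change, and the article gives neither. Simulating it with Normal changes would miss the fallback, because symmetric data go to the t-test.
- *A reader might infer that the fallback is likely to be used for steps/day,* from "mean steps/day 2713 (std. dev. 2190) and mean SBP 141 mm Hg (std. dev. 20 mm Hg"). For steps, zero lies only 2713/2190 = 1.24 standard deviations below the mean, which suggests right-skewed levels. The test is applied to changes, and skewed levels do not imply skewed changes.
- *A reader might infer that a baseline-adjusted model should be primary.* The article makes the unadjusted comparison primary. Whether that is the best choice is a separate question.

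**Conclusion.** The point holds in a narrow form. The test named for skewed data does not make the between-arm comparison that the same sentence requires, and its symmetry assumption conflicts with the skewed case. The error sits in the primary analysis and carries over to all secondary and exploratory outcomes. Its practical size cannot be given: the documents say nothing about the distribution of change-scores, so how often the fallback would be reached is unknown. The conclusion rests only on the stated comparison, the unpaired randomisation and the definition of the signed-rank test. It needs no assumption about effect size, variance or common improvement.

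**What to change.** In the primary-analysis sentence, replace the signed-rank test with *Wilcoxon rank-sum (Mann-Whitney) test of change-scores between arms*. As an option, stratify it by the randomisation factors site and gender (van Elteren test). The unstratified version matches the article's description of the primary analysis as unadjusted.

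Because the secondary and exploratory outcomes refer back to this sentence, the one correction covers them too. The cost is one line of text, with no new data and no change to sample size, power or the order of analyses. It should be made before outcome data are examined by arm.

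### The unadjusted change-score test is made primary on a false ground: chance baseline imbalance shifts its estimate rather than making it conservative, and baseline adjustment would be more precise

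*Protocol article*

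**What the plan says.** The ranking of the analyses is set in the protocol article, Statistical analyses, under the heading on comparing baseline characteristics.

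- **Primary:** the unadjusted difference between arms in change from baseline, by t-test, or by a nonparametric test if the data are skewed. The reason given is that "Imbalance between the treatment arms of characteristics described above would inflate the standard error, making the unadjusted analyses appropriately conservative".
- **Secondary, with a trigger:** analysis of covariance of the change scores. It is introduced by the condition "If, however, we did identify chance differences between the treatment arms in the distribution of the baseline level of the outcome".
- **Sensitivity, with no trigger:** a comparison of follow-up steps/day itself, with baseline as a covariate.
- **Later analyses:** repeated-measures mixed models for the trajectories over time.

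Under Randomization & blinding, allocation uses a "computerized randomization procedure stratified by site and gender". Neither factor enters the primary test. Under Multiple comparisons, change in steps/day is the one endpoint chosen in advance as primary, so this ranking decides the headline result.

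**The concern.** The sentence that justifies the primary analysis treats imbalance as something that only widens the interval. If that were so, the unadjusted test would err on the safe side. But a change score is correlated with its own baseline: people who start low tend to rise and people who start high tend to fall, whatever their treatment. An arm that starts lower by chance will therefore show a larger mean rise with no treatment effect, and an arm that starts higher will show a smaller one.

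Two things are at stake. In the trial that is actually run, the primary estimate may carry a baseline artefact in either direction. And precision that baseline adjustment would supply is lost, although the baseline steps/day are collected for everyone.

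**Working it through.** **Inputs** (Sample size and power): SD 2190 steps/day; "using a 2-sided test with a type I error of 0.05"; 80% power; auto-correlation 0.2; three measurements; effective n 96 per arm; 15% loss to follow-up; within-center correlation 0.0085. The multiplier is 1.960 + 0.842 = 2.802.

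**Step 1: reproduce the plan's figure.**
- Effective n: 120 / (1 + 29 × 0.0085) = 96.3.
- Variance factor for a mean of three measures with correlations 0.2, 0.2 and 0.04: (3 + 4 × 0.2 + 2 × 0.04) / 9 = 0.431.
- Detectable difference: 2.802 × 2190 × √(2 × 0.431 / 96) = 581 steps/day. For systolic pressure (SD 20) the same formula gives 5.3 mm Hg.

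Both published figures reproduce. They describe an average over three measures, not a change score at one visit.

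**Step 2: does imbalance inflate the standard error?** With equal SDs at both visits, the SE of the change-score difference is SD × √(2(1-r) × 2/n). At r = 0.2 and n = 96 this is 2190 × √(1.6 × 2/96) = 400. D does not appear in it.

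A simulation of 20,000 trials with no treatment effect (r = 0.2, 96 per arm) agrees:

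| Intervention arm's baseline relative to control | Mean estimate | Mean SE | Rejection rate |
|---|---|---|---|
| more than 1.5 SE lower | +489 | 399.5 | 17.7% |
| within 0.5 SE | -3 | 399.0 | 1.6% |
| more than 1.5 SE higher | -490 | 399.6 | 16.9% |
| all trials | -4 | – | 5.2% |

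The test is conservative when the arms happen to be balanced and anticonservative when they are not. That is the reverse of the protocol's reasoning.

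**Step 3: size of the shift.** Under no effect, the expected change difference given D is -(1-r)D.
- SE of the baseline difference: 2190 × √(2/96) = 316 (307 with 102 per arm, which is 120 less 15%).
- 1-SE imbalance at r = 0.2: 0.8 × 316 = 253 (245 with 102 per arm).
- 1.96-SE imbalance: 0.8 × 620 = 496.
- The same 1.96-SE imbalance gives 0.5 × 620 = 310 at r = 0.5 and 0.3 × 620 = 186 at r = 0.7.

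**Step 4: precision.** The change-score variance is proportional to 2(1-r) and the baseline-adjusted variance to 1-r². Their ratio, adjusted over unadjusted, is (1+r)/2, so the information lost is 1 - (1+r)/2. Detectable differences below are for 96 per arm at a single time point.

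| r | Information lost | Change score | Baseline-adjusted |
|---|---|---|---|
| 0.04 | 48% | 1,227 | 885 |
| 0.2 | 40% | 1,120 | 868 |
| 0.5 | 25% | 886 | 767 |
| 0.7 | 15% | 686 | 632 |
| 0.8 | 10% | 560 | 531 |

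The protocol gives only 0.2. The value 0.04 (0.2 squared) is what the autoregressive structure in Step 1 implies between T0 and T2. The other rows are assumptions that show the range.

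**The case against.** **The test is valid.** A reader might infer that the primary comparison is biased outright. It is not: over all randomisations the change-score difference is unbiased and the test holds about 5%. The shift is conditional on the imbalance that occurs. This stands, and it limits the fault to conditional bias and lost efficiency. It does not rescue the rationale, because a test with about 5% error is not conservative.

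**The alarming rates belong to a selected tail.** At r = 0.2, if the intervention arm starts significantly lower (about 2.5% of trials), the false-benefit rate is about 27%. That is roughly 0.7% of all trials, inside the nominal 2.5% for that direction. In those trials the covariance analysis would be triggered and set beside the unadjusted means, so readers would see any conflict. This is fair, but the plan would still name the unadjusted figure as the trial's result.

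**Adjustment is already planned.** A reader might infer that it happens only on a trigger. The sensitivity analysis of follow-up steps/day has none. What remains is the ranking.

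**40% is neither a ceiling nor an estimate.** The formula tends to 50% as r falls to zero. The value 0.2 is a planning assumption for auto-correlation, not a reported correlation between baseline and follow-up. A higher true value shrinks both the loss and the shift.

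**Intention to treat and missing data.** A reader might infer a contradiction between a complete-pair t-test and the intention-to-treat claim. The documents do not support it. The article defines the principle by arm ("any subject randomized to the intervention arm remains in that arm"), its analytic overview says missing data will be accounted for, and its Discussion raises unequal follow-up as a possibility, not an expectation.

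**A kernel of truth.** Leaving out prognostic covariates or the stratification factors can leave the SE larger than needed. That is unexplained variance, present whether or not the arms are balanced. The gain from adding site and gender is not quantified here; with a within-center correlation of 0.0085, the part from site may be small.

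**Skewed data.** A mean of 2713 with an SD of 2190 makes skew plausible. The figures above describe the t-test, not the nonparametric alternative.

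**Conclusion.** The rationale is wrong as written, and it decides which result is primary. Chance imbalance does not inflate the standard error of the unadjusted change-score comparison or make it conservative. It displaces the null estimate by -(1-r)D, about 245 to 253 steps/day per 1-SE imbalance and about 496 at 1.96 SE when r = 0.2. For scale, the protocol's stated detectable difference is 581, though that figure rests on the mean of three measures. Unconditionally the test is sound, so the charge is conditional bias and inefficiency, not invalidity.

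The precision loss is 40% at the protocol's own 0.2 and smaller at higher correlations. The sizes assume equal SDs at each visit, a linear relation between baseline and follow-up, and approximately normal means. The direction of the conclusion holds for any r below 1. Baseline and strata adjustment is an improvement that needs no new data.

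**What to change.** 1. Make the primary analysis a model of follow-up steps/day at T1 and T2 with arm, visit, arm-by-visit, baseline steps/day, site and gender. Fit it whatever the baseline comparison shows.
2. Move the unadjusted change-score comparison to sensitivity.
3. Delete the sentence claiming that imbalance makes the unadjusted analysis conservative, and delete the trigger for adjustment.
4. Carry the same change to the secondary and exploratory outcomes, which are to follow the same analysis.

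No new data are needed: baseline steps/day are collected at T0, site and gender are known at randomisation, and baseline-adjusted and mixed models are already in the plan. The cost is a formal amendment, since the trial is under way. It should be dated before anyone sees unblinded outcome data, because a switch made later would itself be data-driven.

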## Methods/Design

This study is a single-blind randomized wait-list controlled trial. Participants are randomized within 4 ethnic-specific clusters at senior centers in Los Angeles to either immediate intervention or 3-month wait list (see Fig. 1). The intervention itself lasts 4 weeks. Measures are taken at baseline prior to randomization (T0), 1-month (T1—for the intervention arm, this is immediately following the 4-week intervention), and 3-months (T2—for the intervention arm, this is 2 months after completion of the intervention). Measures for control group participants are taken at the same time points (1 and 3-months after baseline) while they are still on the wait list; after 3-month data collection, all control arm participants are invited to participate in WTW but do not repeat outcome measures.

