The Worth the Walk intervention consists of a group-based facilitated curriculum with 8 sessions covering topics such as racial/ethnic disparities in stroke and stroke outcomes, what stroke risk factors and warning signs are, blood pressure control, and seeing a healthcare provider regularly. Sessions are 1 h in duration and occur twice weekly for 4 consecutive weeks at a designated senior center. Information in the curriculum on stroke risk factor knowledge is based on materials developed by the American Heart Association/American Stroke Association (AHA/ASA). Special emphasis is placed on physical activity because of its substantial contribution to stroke risk on a population basis [16]. Walking is emphasized as an appealing physical activity based on its association with decreased morbidity and mortality among older adults [27] and the practical reality that walking is an accessible form of physical activity for most seniors.

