### Participants – inclusion and exclusion criteria

We are enrolling an eventual total of 240 participants (60 participants from each of the 4 targeted ethnic groups). Eligibility criteria include: 1) age 60 years or older; 2) self-identifying as the racial/ethnic group for the intervention planned at that site (African American, Latino, Chinese, or Korean); 3) ability to communicate verbally in the appropriate language (English, Spanish, Mandarin, or Korean) in a group setting; 4) ability to sit in a chair and participate in a 1 h discussion session; 5) ability to walk with or without the use of assistive devices such as canes and walkers; 6) available to attend the baseline data collection session and subsequent weekly intervention sessions; 7) has been told by a health care provider that s/he has high blood pressure; 8) able/willing to provide the name of a physician who has seen the potential participant in the past 6 months and provide signed consent for our staff to contact this physician; 9) plans to continue to live in the region during the next 6 months; and 10) cognitive capacity to provide informed consent to participate. Potential participants whose physicians fax a reply card indicating medical contraindication are not eligible (see below under Study procedures, Recruitment section). Potential participants whose physicians fax a reply card indicating no contraindication or do not respond within one week are eligible.

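### The sample size allows for clustering, but the primary t-test ignores it, together with the site and gender strata and the session groups found only in the intervention arm

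*Protocol article*

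**What the plan says.** All references are to the protocol article.

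- **Randomisation.** *Methods/Design* states: "Participants are randomized within 4 ethnic-specific clusters at senior centers in Los Angeles". *Randomization & blinding* adds that site and gender are the strata. The unit is the individual.
- **Delivery.** "The Worth the Walk intervention consists of a group-based facilitated curriculum with 8 sessions" (*Worth the Walk intervention: conceptual basis and development*). Participants report their promises to the group and solve problems together. Two case managers were trained for each site. No group size is given. Controls have no sessions until their 3-month data are in.
- **Sample size.** *Sample size and power* reports that the "intra-class correlation within senior centers was at 0.0085" and, after a clustering adjustment, gives an effective 96 per arm. It does not state the cluster unit, the cluster size or the formula.
- **Primary analysis.** *Comparing baseline characteristics of intervention and control arm subjects* tests the unadjusted difference in change scores by t-test, or a rank test if the data are skewed, and says that "the unadjusted analyses will serve as the primary results of the trial". Covariate adjustment is secondary and depends on a chance imbalance. The mixed models in that section concern trajectories over time and are not primary.

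**The concern.** The two sections assume different things. The sample size section says that participants are correlated and pays for it. The primary test says that they are independent.

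The test leaves out two features of the design:

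- **Session groups.** People who share a leader, eight sessions and a group process may change together. This can happen in the intervention arm only. Ignoring it makes the standard error too small and the test too liberal.
- **Strata.** Site and gender were balanced by design but are left in the error term. This makes the standard error slightly too large, so the test is conservative and loses precision.

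The article defends the unadjusted test as conservative. That argument is about baseline imbalance. It does not cover session-group correlation, which acts in the opposite direction.

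**Working it through.** **Inputs from the article.** "we plan to enroll 240 subjects from 4 senior centers"; "60 participants from each of the 4 targeted ethnic groups"; 120 per arm, hence 30 per arm per center; "using a 2-sided test with a type I error of 0.05"; 80% power; SD 2190 steps/day; 15% not completing follow-up; ICC 0.0085 within senior centers.

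**Assumptions.** Session-group size m is not stated; I use 8 to 30. At m = 30 each site's whole intervention arm is one group. The session-group ICC is not stated either. I first borrow 0.0085, although that figure is for centers.

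**1. Reproducing the plan's 96.** Effective n = n / [1 + (m − 1) × ICC].

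- 120 / (1 + 29 × 0.0085) = 120 / 1.2465 = 96.3.
- 102 / (1 + 7 × 0.0085) = 102 / 1.0595 = 96.3, where 102 = 120 × 0.85.

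Both routes give 96, so the article's text does not settle which unit or size was used.

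The detectable effect reproduces with three measures and first-order autocorrelation 0.2. The variance factor is f = [3 + 2 × (2 × 0.2 + 0.04)] / 9 = 0.4311, and 2.8016 × 2190 × √(2 × 0.4311 / 96) = 581.5 steps/day, against the stated 581.

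**2. Session groups in one arm.** Design effect DE = 1 + (m − 1) × ICC in the intervention arm and 1 in the control arm. The true variance of the arm difference, relative to what the t-test assumes, is R = (1 + DE)/2. Type I error = 2Φ(−1.96/√R).

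| ICC | m | DE | R | Type I error |
|---|---|---|---|---|
| 0.0085 | 8 | 1.0595 | 1.030 | 5.3% |
| 0.0085 | 15 | 1.119 | 1.060 | 5.7% |
| 0.0085 | 30 | 1.2465 | 1.123 | 6.4% |
| 0.05 (assumed) | 8 | 1.35 | 1.175 | 7.1% |
| 0.05 (assumed) | 15 | 1.70 | 1.35 | 9.2% |
| 0.05 (assumed) | 30 | 2.45 | 1.725 | 13.6% |

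A simulation (4 sites, 30 per arm per site, 40,000 runs) agrees. At ICC 0.0085 it gives 5.6% for groups of 10, 5.7% for 15 and 6.4% for 30.

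**3. Omitted site.** Balance by site removes the shared center component from the arm difference, but the t-test keeps it in its error term. At ICC 0.0085 the variance ratio is 1 − 0.0085 = 0.9915, and 2Φ(−1.96/√0.9915) = 4.9%. The simulation gives 4.8% with center clustering alone. With center and session-group clustering together (groups of 30) it gives 6.3%, so at this ICC omitting site barely offsets the inflation. The article gives no figure for gender.

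**4. Does the power allowance cover one-arm clustering?** Effective n = n/R at ICC 0.0085, m = 8 to 30:

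- from 120 per arm: 117 down to 107, above 96;
- from 102 per arm: 99 down to 91; it reaches 96.3 at m = 15, so the allowance suffices only for groups up to about 15.

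**5. Number of groups.** 120/m gives 15, 12, 8 and 4 groups for m = 8, 10, 15 and 30. With four groups, one per site, and site fixed effects, about 3 degrees of freedom remain. The two-sided 5% critical value is then 3.18 instead of 1.96.

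**The case against.** The strongest defence has four parts.

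- **The effect is small.** At the only ICC in the article the test stays between about 5.3% and 6.4%. This stands.
- **Group correlation is itself a product of treatment.** If the program changes nobody's walking, correlation produced by shared leaders and promises is absent and the t-test is not inflated. This stands as a qualifier: the rates above apply when group effects vary around an average of zero. Interval width can be wrong in either case.
- **Model detail belongs in an SAP or full protocol.** This holds for the random-effect structure. It does not remove the inconsistency, because the article itself names the test and declares it primary.
- **Site is not forgotten.** *Process evaluation* will examine variation in effectiveness among the four sites. That does not enter the primary standard error.

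A reader might also infer three stronger things that the article does not support:

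- **That 96 is a mistaken center deflation and should be removed**, taking 581 to 520 steps/day at 120 per arm. The derivation is inferred, since 102 with m = 8 gives the same 96.3. Within-center randomisation cancels the shared center effect but not variation of the treatment effect between centers. Each center has its own ethnic group and leaders, and two of the eight sessions are tailored by ethnic group. A one-arm session-group effect also needs an allowance.
- **That the test runs at 7% to 14%.** This needs an ICC of 0.05, about six times the documented value and without a source in the article. The top of the range also needs a single group of 30 at every site.
- **That omitting site inflates false positives.** It makes the test conservative.

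**Conclusion.** The point holds as an inconsistency of modest size. The article allows for clustering when it sizes the trial, then names a primary test that assumes independence and ignores both the strata and the one-arm session groups.

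The type I error is about 5.3% to 6.4%, given a session-group ICC equal to the center value of 0.0085, groups of 8 to 30, and group effects that vary around zero. It is higher only if the session-group ICC is larger, which the article neither states nor excludes. Omitting site costs under 1% in variance at that ICC. The cost could be larger here because each site is a different ethnic group, whereas the ICC comes from earlier studies of older Latinos and African Americans.

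The existing allowance probably covers the power loss if 120 per arm is the right base. It does nothing for the error rate of the test.

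**What to change.** 1. **Primary analysis.** Replace the unadjusted t-test with a model of change in steps/day with treatment arm, site and gender as fixed effects. The unadjusted comparison can stay as a supporting analysis.
2. **Session group.** Add a random effect for session group in the intervention arm only, with controls as singletons (a partially nested model) and small-sample degrees of freedom. If there will be only about four groups, make this a pre-specified sensitivity analysis instead. Fix that choice before outcome data are seen.
3. **Data.** Record a session-group identifier with the attendance that is already taken.
4. **Sample size text.** State the cluster unit, the cluster size and the formula behind 96, with the planned session-group size and a range for its ICC, so that the allowance matches the analysis. Do not simply delete it.

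**Cost.** Wording, one extra data field and slightly more modelling; enrolment and treatment do not change. Site and gender terms are essentially free. Carrying session group into the standard error widens intervals: slightly with many small groups, possibly by a lot with four (critical value 3.18 against 1.96).
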